### Results: description of the final features

The main features of the final audit, feedback and gamification interventions are listed in Table 4 and illustrated in Figure 4. All features are accessible within MacPLUS FS on a `reputation tab’ (Figure 4A). We generated about 50 badges rewarding the following behaviors: total and weekly frequencies of searches, frequencies of access to the top layers of the EBM resource pyramid (summaries), to the middle layers (pre-appraised research), and to bottom layers (non-pre-appraised research), number of complementary resources accessed per search, number of alerts to new evidence accessed, number of questions recorded (for users also allocated to the Clinical Question Recorder), and number of videos watched (for those allocated to the Evidence Retrieval Coach).

**Figure 4 Fig4:**
[figure not shown]
**Illustration of the components of the Audit, Feedback & Gamification. A** - **E**: For a detailed description of each feature displayed, see the result section in the section "Intervention C - audit, feedback and gamification.

Each badge was assigned a reputation score based on the desirability of the behavior it reinforces. Badges pop-up online after a specific behavior (Figure 4E), award their reputation score to the user, and can be accessed again later (Figure 4D). Clinician’s resulting reputation score can be compared to peers’ through percentiles displayed in interactive pictographs (Figure 4B), and followed graphically across time (Figure 4C). Finally, clinicians can explore their access to each EBM resource, mapped according to the EBM pyramid (Figure 4A).

### III. Protocol of the randomized controlled trials

#### Setting and study participants

We will conduct the trials described in this protocol in the teaching hospitals and clinics affiliated with McMaster University, Ontario, Canada. This amounts to 2 major academic hospital systems, operating 10 hospitals in the Hamilton area, as well as 2 regional campuses in Niagara and Waterloo, Ontario.

Currently about 2,800 clinicians and students are registered in MacPLUS FS. The first trial will be conducted among all postgraduate trainees, and the second trial among all faculty registered in MacPLUS FS at the beginning of the trials, after exclusion of those no longer physically working at McMaster University affiliated hospitals. We will also exclude registrants who have never interacted with MacPLUS FS, either by logging in to read email alerts or to perform a search, during the last 12 months counting back from the beginning of the trials, regardless of how long they have been registered. These broad eligibility criteria reflect our choice to perform pragmatic effectiveness trials, rather than focusing only on high-frequency users. Indeed, our objective is precisely to increase the quantity and quality of searches among low-frequency users in real clinical practice. Nevertheless, we are excluding registrants with a very high probability of being unexposed or insensitive to our web-based interventions, either because they are no longer at our institution or have repeatedly ignored MacPLUS FS over a prolonged period.

By December 31, 2013, these eligibility criteria were met by 904 clinicians - 429 postgraduate and 475 faculty MDs (see Table 5) - after exclusion of 211 registrants no longer working at McMaster University, and 284 who never interacted with MacPLUS FS during the last year. About two-thirds of eligible users interacted with MacPLUS FS only through email alerts, while one-third performed at least one search in that period. About 16% of eligible clinicians work in the field of internal medicine, 32% work in family medicine, while the other half of the sample works in a wide array of other specialties (see Table 5).

**Table 5 Tab5:** **Baseline utilization among the eligible 904 MDs during the six months prior to the trial**

	Postgraduates	Faculty	Total MD
	(n = 429*)	(n = 475*)	(n = 904*)
**Specialty type** - n (%)			
Internal Medicine	82 (19.1%)	66 (13.9%)	148 (16.4%)
Family Medicine	107 (24.9%)	184 (38.7%)	291 (32.2%)
Other Specialties	240 (55.9%)	225 (47.4%)	465 (51.4%)
**Total number of searches**	935	423	1,358
**Searches/month/user** - Mean (SD)	0.46 (1.42)	0.20 (0.83)	0.32 (1.16)
**Categories of search frequency** - n (%)			
>5 *(Super-searchers)*	8 (1.9%)	4 (0.8%)	12 (1.3%)
1 to 5 *(Regular-searchers)*	45 (10.5%)	24 (5.1%)	69 (7.6%)
<1 *(Occasional-searchers)*	89 (20.7%)	72 (15.2%)	161 (17.8%)
0 *(Alert-only-users)*	287 (66.9%)	375 (78.9%)	662 (73.2%)
**Time since last search** - n (%)			
<= 365 days	163 (38.0%)	143 (30.1%)	306 (33.8%)
>365 days	266 (62.0%)	332 (69.9%)	598 (66.2%)
**Total number of e-mail alerts read**	4,064	7,092	11,156
**E-mail alerts read/month/user** - Mean (SD)	1.65 (2.99)	2.54 (6.03)	2.12 (4.85)
**Total number of other weblogins**	1163	740	1903
**Other weblogins/month/user** - Mean (SD)	0.52 (4.10)	0.32 (2.85)	0.41 (3.50)

*Four additional participants (two postgraduates and two faculty) are missing from this count, as they registered in Jan 2014, just before the beginning of the trial.

### Randomization

Participants will be randomized to our three web-based interventions in a factorial design (see overview of study design and Table 2). Postgraduates and faculty MDs will be randomized separately and further stratified according to time since last search (<= 365 days vs. >365 days; see Table 5), as an overall proxy of their baseline frequency searches in MacPLUS FS. Right before the beginning of the trials, participants will be randomly allocated to each factorial group (2^3^ = 8 groups), balancing on blocks of 16 within each stratum (=2 - 8). Our information technology programmers, in charge of MacPLUS FS system administration, will perform randomization using a computer-based pseudo-random number generator. They will maintain a secure master list of the randomization codes and assignments, and conceal allocation from the analysts.

### Blinding and control group

Although participants cannot be blinded to the interventions, they will not be informed of the different interventions that are being offered. In addition, all participants, including the control group with no intervention, will be exposed to new minor features one month prior to the beginning of the trial. These include: small changes in the web design (simplification of available tabs and navigation), waiting time features displaying all resources searched in parallel in MacPLUS FS (see Figure 1), and a novel `single citation matcher’ (see Table 1). These minor new features would thus further minimize the risk of contamination between the intervention arms from users becoming aware of interventions they are missing. Moreover, the interventions cannot be shared, as they are linked to individuals’ accounts, so that it is unlikely that registrants who are not offered an intervention would increase their utilization just by hearing about it.

### Outcomes

#### Primary outcome

Our primary question is whether each intervention increases the quantity of searches to answer questions - *i.e*., search utilization (not counting logins to e-mail alerts or to access other resources). This will be measured by (i) rate of searches/month/user, (ii) and corresponding proportions of `super-searchers’ (>five searches/month), `regular-searchers’ (one to five searches/month), `occasional-searchers’ (<one search/month), and `alert-only-users’ (no searches/month). The primary outcome will be averaged over six months, but continuously recorded as participants will be signed on through their individual user account that tracks logins and use of EBM resources, down to individual keystrokes.

Table 5 shows the baseline utilization data during the six months prior to the start of the trial, from July to December 2013. Postgraduates MDs (n = 429) searched MacPLUS FS 935 times in total, corresponding to about 0.46 searches/month/user, whereas they accessed 4,064 alerts to new evidence, corresponding to 1.65 alerts/month/user, and consulted other web-resources in MacPLUS FS 0.52 times/month/user. About 66.9% of postgrads users were `alert-only-users,’ while 10.5% were `regular-searchers’ and 1.9% `super-searchers.’

The utilization patterns were different for Faculty MDs (n = 475) who searched MacPLUS FS half as much, about 423 times in total, corresponding to about 0.20 searches/month/user, whereas they accessed almost twice as many alerts to new evidence, 7,092 alerts in total, corresponding to 2.54 alerts/month/user, and consulted other web-resources in MacPLUS FS 0.32 times/month/user. About 78.9% of faculty used were `alert-only-users,’ while 5.1% were `regular-searchers’ and 0.8% `super-searchers.’

### Secondary outcomes and questions

We will assess whether each intervention can increase the utility of the evidence retrieved (satisfaction in meeting users’ information needs, expected impact on one’s general practice), the use of the evidence (the extent of use when caring for a specific patient), and its perceived usefulness in patient care and outcomes (perceived benefits of applying the evidence for a specific patient). Utility, use and usefulness of the evidence retrieved will be assessed using an adapted version of the Impact Assessment Method (IAM) [41]-[43], which was specifically developed for assessing how clinicians use information, based on the Acquisition-Cognition-Application-Outcome Model [42]-[44]. This validated six-item questionnaire takes less than one minute to complete online and will be sent by e-mail for online completion following a pre-defined automatic algorithm. The first invitation will be sent out one month after the participant’s first online exposure to one or more interventions, with one reminder after 24 hours. The next invitation will be sent following the next search, but after a two-week delay. This process will be repeated until one filled questionnaire for a clinical question is returned, or the trial ends (see details and full questionnaire in Additional file 3). Perceived usefulness will be analyzed as the `number needed to benefit from evidence,’ defined as the number of patients for whom the evidence has to be retrieved to observe or expect health benefits for one patient [45]*.*

Other secondary questions that we plan to address include whether each intervention efficacy varies across time within the six-month trial (*e.g*., persistent, transient, increasing or decreasing effect), and whether the interventions have an impact on non-searching utilization of MacPLUS FS (*i.e*., frequency of alerts read, frequency of web logins for other clinical resources).

Finally, we will explore if the interventions modify the patterns of use of the different EBM resources, and in particular if they increase the accesses to higher levels of evidence, such as summaries and pre-appraised research, compared to non-pre-appraised research. Table 6 displays the baseline distribution of access across the pyramid of EBM resources among clinicians that have adopted MacPLUS FS, that is, `regular-searchers’ and `super-searchers.’ With 1,025 searches, these users have conducted about 75% of all searches in MacPLUS FS, and accessed one of its resources 1,390 times in total. All resources in the federated search were consulted: summaries were accessed 53.2% of the times, pre-appraised research in 16.1%, and non-pre-appraised research in 30.6% of the times. Postgraduates searched less summaries than faculty did (49.0% vs. 63.8%), and more non-pre-appraised resources (35.3% vs. 19.3%).

**Table 6 Tab6:** **Baseline frequency of access to EBM resources (% of all accesses), among `regular-searchers’ and `super-searchers’***

		Postgraduates	Faculty	Total
		(n = 53)	(n = 28)	(n = 81)
		739 searches	286 searches	1,025 searches
**Summaries**		**485 (49.0%)**	**255 (63.8%)**	**740 (53.2%)**
	DynaMed	174 (17.6%)	39 (9.8%)	213 (15.3%)
	UpToDate	120 (12.1%)	128 (32.0%)	248 (17.8%)
	Best Practice	147 (14.8%)	71 (17.8%)	218 (15.7%)
	ACP PIER	44 (4.4%)	17 (4.3%)	61 (4.4%)
**Pre-appraised research**		**156 (15.8%)**	**68 (17.0%)**	**224 (16.1%)**
	Synopses of systematic reviews	23 (2.3%)	17 (4.3%)	40 (2.9%)
	Systematic reviews	66 (6.7%)	21 (5.3%)	87 (6.3%)
	Synopses of studies	10 (1.0%)	4 (1.0%)	14 (1.0%)
	Studies	57 (5.8%)	26 (6.5%)	83 (6.0%)
**Non-pre-appraised research**		**349 (35.3%)**	**77 (19.3%)**	**426 (30.6%)**
	Filtered studies	257 (26.0%)	60 (15.0%)	317 (22.8%)
	Unfiltered studies	92 (9.3%)	17 (4.3%)	109 (7.8%)
**Total number of accesses**		**990 (100%)**	**400 (100%)**	**1,390 (100%)**

**i.e*., clinicians who conducted more than one search per month on average.

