**Table 2 Tab2:** **Factorial randomization scheme of the three interventions**

Interventions*			
A	B	C	Random group allocation
*Clinical Question Recorder*	*Evidence Retrieval Coach*	*Audit, Feedback & Gamification*	
**1**	**1**	**1**	Group 1
**1**	**1**	0	Group 2
**1**	0	**1**	Group 3
**1**	0	0	Group 4
0	**1**	**1**	Group 5
0	**1**	0	Group 6
0	0	**1**	Group 7
0	0	0	Group 8

*For each intervention, half of the sample is randomized to receiving the intervention [1] and the other half to not receiving it [0]. All factorial combinations of the intervention result in eight allocation groups (2^3^ = 8).

In the next section, we describe the development of the three interventions: our theoretical framework; user-testing of their different iterations; and the final features that we will test in the trials. The third section details the methodology of the factorial randomized controlled trials.

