### Analysis of secondary questions

An exploratory analysis will investigate time trends in intervention efficacy. Rather than using the average number of searches per user per month over the six months of the trial, we will conduct a longitudinal analysis using the number of searches per user for each of the six months of the trial as the dependent variable, regressed onto time, dummy variables for each of the interventions, the interaction between time and intervention, together with search frequency at baseline. This regression model will be fitted using a Generalized Estimating Equation (GEE).

Finally, we will compare the distribution of answers on the IAM questionnaire *(i.e*., utility, use and usefulness of the evidence retrieved), as well as the distribution of access to the different EBM resources, using chi-squared tests.

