### Trial administration and data management

The trials will be conducted at the Health Information Research Unit, at McMaster University, which designed and is hosting MacPLUS FS. Before the trials start, research staff [name] and the principal investigator [name] will check eligibility criteria of the registrants, verify their affiliation to McMaster, profession and training level, and crosscheck the information stated at registration with official administrative medical databases.

The administration of interventions, outcome measurements, and the sending of periodic online IAM questionnaires will all be programmed before randomization and further handled automatically as they will be built into the MacPLUS FS online infrastructure.

The trials will start simultaneously for all participants. All interactions with MacPLUS FS, including any click-through links within emails, will automatically sign participants on through their individual user account that tracks logins and use of EBM resources. Primary and secondary outcomes will be recorded from this automatic monitoring of the system, and stored in a specific and secure database within MacPLUS FS.

The research staff [name] and the principal investigator [name] will review overall utilization data collected on a weekly basis, looking for completeness of data and navigational bugs. However, no interim analysis will be performed before the trial end.

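### As written, the impact-questionnaire clock starts at first exposure to an intervention, which leaves the no-intervention group without a starting event and unbalances the factorial comparison of the secondary questionnaire outcomes

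*Protocol article*

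**What the plan says.** The secondary-outcomes section sets out to assess the effect of each intervention on utility, use and perceived usefulness, measured by the IAM. It fixes the invitation process in three steps:

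- The first invitation is timed one month from the participant's "first online exposure to one or more interventions, with one reminder after 24 hours".
- Each later invitation waits for a further search by the user and a gap of two weeks.
- The cycle stops at one completed questionnaire about a clinical question, or at the end of the trial.

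The same section refers to Additional file 3 for details of the algorithm and the questionnaire.

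On the design, the footnote to Table 2 says "All factorial combinations of the intervention result in eight allocation groups", and the table gives Group 8 the code 0/0/0. The section on blinding and control group says that "all participants, including the control group with no intervention, will be exposed to new minor features one month prior to the beginning of the trial". Those features precede the trial, go to everyone, and are not interventions A, B or C.

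On the analysis, the section on secondary questions says "we will compare the distribution of answers on the IAM questionnaire" with chi-squared tests, and mentions no adjustment for the other two interventions. The section on trial administration says "The trials will start simultaneously for all participants". That gives a common clock, which the IAM rule does not use.

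**The concern.** A participant in Group 8 meets no intervention, so under the stated rule the first invitation never falls due. The later invitations are defined only as steps after the first, and no other part of the article gives this group a route into the questionnaire. If the rule is followed literally, the IAM data lack the untreated cell.

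In the other seven groups the start can depend on what was allocated and on what the user does. Videos appear on behavioural triggers or by weekly e-mail, badges follow particular behaviours, and the recorder depends on the clinician engaging with it. A user with three interventions has more ways to start the clock than a user with one. The time left for repeat invitations, and so the chance of ever answering, may then differ by arm after randomisation.

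The IAM outcomes are the secondary outcomes named in the abstract. The Discussion also makes a substantial effect on evidence use and usefulness part of the justification for a larger trial, so a distorted IAM comparison would feed into that decision.

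**Working it through.** **Inputs.** Table 2: eight groups coded A/B/C. Table 5: 429 postgraduates and 475 faculty. Secondary-outcomes section: the invitation rule. Section on analysis of secondary questions: chi-squared tests. Assumptions made here: additive effects a, b and c on the percentage of favourable answers, equal cell sizes, and equal response in every invited cell.

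**Step 1: the plan's own layout.** 2³ = 8 groups. Each intervention is on in four and off in four, and within each side the other two are present in 2 of 4 groups (50%). The marginal difference for A is (a + b/2 + c/2) − (b/2 + c/2) = a. The half-against-half layout reproduces.

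**Step 2: apply the invitation rule as written.** Group 8 drops out.

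| Side of A | Groups | B present | C present |
|---|---|---|---|
| On | 1, 2, 3, 4 | 2/4 = 50% | 2/4 = 50% |
| Off | 5, 6, 7 | 2/3 = 66.7% | 2/3 = 66.7% |

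By symmetry the same table holds for B and for C.

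**Step 3: number of users without a starting event.** 429/8 = 53.6 postgraduates and 475/8 = 59.4 faculty, about 54 and 59. That is one eighth of each trial and one quarter of every 'off' half. These are randomised users, not expected respondents.

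**Step 4: what an unadjusted margin then estimates.**

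On side: a + b/2 + c/2. Off side: 2b/3 + 2c/3.

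Difference: a + (1/2 − 2/3)b + (1/2 − 2/3)c = a − (b + c)/6.

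- All three effects equal (a = b = c): a − 2a/6 = 0.67a, so two thirds of the true effect is seen.
- Only B works (a = c = 0): the contrast for A is −b/6. For an assumed b of 10 points it is −1.7 points; for 30 points, −5.0 points.

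**Step 5: sampling error for scale.** Table 5 shows 8 + 45 + 89 = 142 postgraduates and 4 + 24 + 72 = 100 faculty with at least one search in the six baseline months. Suppose that many users answered, spread evenly over the eight groups. The contrast for A would be 4 × 142/8 = 71 against 3 × 142/8 ≈ 53 postgraduates, and 50 against 37.5 faculty. With proportions near 50%, the standard error is √(0.25/71 + 0.25/53) = 9.1 points and √(0.25/50 + 0.25/37.5) = 10.8 points.

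**Step 6: with a trigger common to all eight groups.** The comparison returns to Step 1, and the marginal difference equals a under the same assumptions.

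The effect of differing invitation times cannot be computed, because the article gives no distribution of first-exposure times.

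**The case against.** The strongest objection is that the article condenses an algorithm whose details sit in Additional file 3. That file may give controls a start date. The ethics section says all registrants agree to receive periodic questionnaires, and nowhere are controls said to be excluded. A reader might infer that Group 8 was in fact never invited; the documents do not support that as a certainty. What stands is that the article states an explicit rule, and the rule yields no invitation for Group 8.

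A reader might also infer that the factorial comparison is broken. That is too strong, for two reasons:

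- The plan does not say that the chi-squared tests compare halves. Its half-against-half sentence concerns the primary hypotheses. If the allocation groups themselves were compared, nothing would leak between interventions.
- Additive main effects remain estimable from seven cells, and the plan expects additivity. Still, the IAM aim is worded for each intervention, and no adjusted IAM analysis is stated.

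The size rests on an assumed effect, and on the baseline figures in Step 5 it stays below one standard error throughout. That objection stands as to size. It does not make the contrast correct, because a systematic shift does not shrink as more users answer.

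The divergence in timing is unquantified. The trigger is exposure, not engagement, and the weekly e-mails for B may start many clocks early. So the timing point can be stated only as a possibility.

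Finally, the Discussion already warns of low survey response and likens the study to a phase II trial. That lowers the weight of the point but does not answer it.

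**Conclusion.** The point holds in a limited form. Taken as written, the IAM rule has no starting event for the no-intervention group and lets the start vary with allocation and behaviour in the other seven. Unless the additional file supplies a start date for controls, each comparison is four groups against three, with the other interventions at 50% against 67%.

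If each intervention's margin is tested without adjustment, the estimate is off by −(b + c)/6, given additive effects, equal cells and equal response. The 1.7 to 5.0 points are an illustration, not a prediction. A model with all three intervention terms would remove this imbalance under additivity. It would not restore the untreated reference or the three-way interaction, and it would not correct for differing invitation times or for who responds.

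Only the secondary IAM outcomes are concerned. The primary outcome is logged automatically for every user, and nothing here bears on it.

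**What to change.** 1. State how Group 8 is handled in the invitation algorithm, in the article's own text as well as in the additional file.
2. Time the first invitation for all eight groups from the common trial start, for example at day 30, conditional neither on exposure nor on a search. Searching is what the interventions aim to change, so a search-based first trigger would bring allocation back into who is invited. The existing two-week rule can follow unchanged. It and non-response will still leave some selection, which should be acknowledged.
3. Analyse the IAM answers in one model with terms for all three interventions, instead of separate unadjusted chi-squared tests.
4. Also report the proportion with a reported use, and with a reported benefit, over all randomised users. Do this only if Group 8 is invited; otherwise its zeros arise by design, and the summary should be confined to the seven invited groups.
5. The article says the trial is ongoing and analysis has not begun. If invitations already sent cannot be changed, keep the joint model, state that the no-intervention cell is missing, and limit the IAM conclusions accordingly.

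The cost is a change to the automatic e-mail trigger, a revised analysis sentence, and about one seventh more first invitations (8/7 − 1). If the trigger changes during the trial, the report must note that two invitation rules were used.
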